### Blinding

Both investigators and participants will be blind with respect to the treatment conditions. Participants will be informed that two different colours of light (white-yellowish and green) will be compared, but not that a placebo condition is present, nor that the green light is less bright or less effective compared to the white-yellowish lamp. This approach is effective in avoiding differences in participants’ expectations regarding the effectiveness of the conditions, as expectations may affect treatment effects [30, 53, 54]. The investigators involved in data acquisition will be blind to the conditions, as the lamps will be delivered at the participants’ homes by independent research assistants, who are instructed not to discuss the brightness of the lamp, and participants will be instructed not refer any details of their condition to the investigators. A similar blinding procedure showed to be successful in a previous study conducted by our institute [30].

To evaluate the blinding procedure, participants’ expectations of the effect of light therapy on depressive symptoms will be measured before installation of the light therapy lamps, using an adapted version of the expectations questionnaire developed by Lieverse and colleagues, 2011 [30].

### Study setting

Test visits will be carried out at clinical research units of two locations of the VU University Medical Centre: Amsterdam and Hoorn, The Netherlands.

### Outcome measures

Outcome measures will be evaluated just before the start of the intervention (T0), after 4 weeks of light therapy (T4) and after 4 weeks of follow-up (T8). Changes in outcome measures (T0 – T4, T4 – T8, or T0 – T8) will be compared between the two study conditions. Additionally, several outcome measures will also be evaluated weekly during the intervention period (T0, T1, T2, T3, T4, T8) to allow for analysis or temporal changes in these measures. A schematic overview of the outcome measures is depicted in Table 1.

**Table 1 Tab1:** Outcome measures

Weeks relative to start intervention (T)			0	1	2	3	4	5	6	7	8
Visits		S	1				2				3
Telephone contact				1	2	3			4		
Run-in phase		X-es	X-es								
Intervention phase				X-es	X-es	X-es	X-es				
Follow-up phase								X-es	X-es	X-es	X-es
Participant characteristics	Psychiatric diagnosis, seasonality, chronotype, sleep apnoea, medical history, current medication, biochemical blood tests, sociodemographic factors	X	X								
Psychometrical measures	Depressive symptoms		X	X	X	X	X				X
	Anxiety symptoms		X	X	X	X	X				X
	Diabetes-related distress		X				X				X
	Quality of life, disability		X				X				X
Glucometabolic measures	Insulin sensitivity		X				X				
	HbA1c level		X				X				X
	Fasting glucose level		X				X				X
	Hypoglycaemic events		X	X	X	X	X				X
Circadian mediating factors	Diurnal HPA axis activity		X				X				X
	Objective sleep		X				X				X
	Subjective sleep		X	X	X	X	X				X
Other factors	Body weight, body mass index, waist-hip ratio, body composition		X				X				X
	Physical activity		X				X				X
	Autonomic nervous system function		X				X				X
Safety	Adverse effects		X	X	X	X	X				X
	Ophthalmological examination	X									X
Compliance	Participant-report compliance			X	X	X	X				
	Light meter		X				X				X

*Abbreviations*: *S* screening, *HPA* hypothalamic-pituitary-adrenal

#### Participant characteristics

Various participant characteristics will be obtained before the start of the light therapy (S, T0): psychiatric diagnosis in the category of mood and anxiety disorders according to DSM-IV criteria as assessed using the CIDI WHO version 2.1 [43]; seasonality of depression [55]; chronotype [24]; presence of sleep apnoea [56]; medical history; current medication; biochemical blood tests; and sociodemographic factors. These participant characteristics allow for the characterisation of our study sample.

#### Primary outcome measures

Depressive symptoms will be assessed by the self-report version of the Inventory of Depressive Symptomatology (IDS) (T0, T1, T2, T3, T4, T8) [57]. The IDS allows for profiling of depression, as the questionnaire discriminates directions of the weight, appetite, sleep and psychomotor symptoms, and can be used to determine depression severity. Scores between 14 and 25 indicate mild depression; scores between 26 and 38 indicate moderate depression; scores between 39 and 48 indicate moderate to severe depression; and scores of 49 and greater indicate severe depression. A reduction of 50 % or greater of the baseline depression score is regarded as a clinically significant reduction in depressive symptoms. Depression remission is *a priori* defined as an IDS score of 13 or less.

Insulin sensitivity will be evaluated at the baseline visit (T0) and the visit following light therapy (T4) in a subsample of 60 participants. Insulin sensitivity will be quantified using a hyperinsulinaemic-euglycaemic clamp procedure, the gold standard for the quantification of whole-body insulin sensitivity. This procedure quantifies the rate of exogenous glucose infusion required to maintain the plasma glucose concentration at euglycaemic levels in response to a fixed increase in the plasma insulin level. Because 80–90 % of the infused glucose is taken up by skeletal muscle under conditions of euglycaemic hyperinsulinaemia, insulin sensitivity measured with this procedure primarily reflects that of skeletal muscle [58]. The hyperinsulinaemic-euglycaemic clamp procedure is performed as previously described by DeFronzo and colleagues [59]. Briefly, participants will be admitted at our research unit following an overnight fast. They are placed in a semi recumbent position during the procedure. A cannula will be inserted into a vein in the antecubital fossa for infusion of glucose and insulin. Insulin (Novorapid 100 IU/ml; Novo Nordisk, Bagsvaerd, Denmark) will be continuously infused at a rate of 40 mU/m2*min, which creates a hyperinsulinaemic state, which will largely decrease endogenous glucose production by the liver. A contralateral dorsal hand or wrist vein will be cannulated and maintained at 50 °C to permit sampling of arterialised venous blood for bedside measurement of blood glucose concentrations (Yellow Springs Instrument 2300 STAT Analyser, Yellow Springs, Ohio, Unites States of America) every 5 min. Glucose (20 %) will be infused at a variable rate to maintain blood glucose levels at 5 mmol/L. When a stable blood glucose level of 5 mmol/L is achieved (minimally after 90 min of insulin infusion), the blood glucose level will be kept at this level for 30 min (steady state). At this point the glucose infusion rate equals the skeletal muscle glucose uptake. The M-value (expressed as the amount of glucose infusion in mol/kg*min) will be calculated over this steady state period as described previously [59]. Blood samples for measurement of plasma insulin concentrations will be obtained at several time points before and during insulin infusion.

#### Secondary outcome measures

Secondary participant-reported outcome measures include anxiety symptoms, as anxiety symptoms often co-occur with depressive symptoms; diabetes-related distress; and quality of life and disability, as these measures are increasingly important when evaluating new treatments in clinical trials. Anxiety symptoms are evaluated using the Beck Anxiety Inventory (T0, T1, T2, T3, T4, T8) [60], diabetes-related distress is measured using the Problem Areas In Diabetes questionnaire (T0, T4, T8) [61], quality of life using the EuroQol-5 Dimensions questionnaire (T0, T4, T8) [62] and disability using the Sheehan Disability Scale (T0, T4, T8) [63].

Glucometabolic secondary outcome measures will include the clinically relevant glycated haemoglobin A1c (HbA1c) level (T0, T4, T8), fasting plasma glucose level (T0, T4, T8), and number of hypoglycaemic events as reported in the diary (T0, T1, T2, T3, T4, T8).

#### Circadian mediating factors

Mediating factors that reflect circadian rhythmicity will include diurnal HPA axis activity, objective accelerometer measures of sleep duration and subjective measures of sleep duration and quality.

Diurnal HPA-axis activity is assessed by free cortisol assessment using six saliva samples per day (T0, T4, T8). The morning cortisol awakening responses will be assessed by four saliva samples in the morning: after awakening, plus 30 min, plus 45 min and plus 60 min. Cortisol levels in the evening will be obtained from two saliva samples in the evening at 10 and 11 pm. Saliva samples will be collected at home, using cotton swaps (Salivette, Sarstedt, Nümbrecht, Germany) that will be stored in the refrigerator. Participants will bring the samples with them to the research facility where the saliva will be centrifuged and stored at −80 °C for analysis.

Objective measures of sleep will be obtained using a microelectromechanical system (GENEActiv, Activeinsights Ltd, Kimbolton, United Kingdom), an accelerometer that can reliably measure sleep-wake behaviour [64] and will be worn for one week continuously. Estimates of sleep parameters will be obtained from these data using a previously validated algorithm [64].

Subjective sleep parameters will be scored using the Pittsburg Sleep Quality Index (T0, T4, T8) [65], the Insomnia Severity Index (T0, T2, T4, T8) [66, 67] and a sleep diary (T0, T1, T2, T3, T4, T8) [68].

#### Other factors

Other potential mediating or confounding factors include body weight, body mass index, waist-hip ratio, body composition, physical activity and autonomic nervous system function. Body composition will be measured by bioelectrical impedance analysis (T0, T4, T8), physical activity will be measured using a wrist-worn accelerometer (T0, T4, T8) and autonomic nervous system function will be evaluated with spectral analysis of the heart rate variability (T0, T4, T8). Whole blood (T0, T4), plasma and serum (T0, T4, T8) will be collected and stored for future additional research questions that require additional biochemical or DNA analyses.

#### Safety and tolerability of light therapy

Adverse effects of light therapy will be assessed, using a self-report adverse effects questionnaire (T0, T1, T2, T3, T4, T8) that is based on the side effect interview from Lieverse and colleagues, 2011 [30, 69]. The following items will be assessed: tired eyes, dry eyes, painful eyes, visual impairment, headache, early morning awakening, fatigue, drowsiness, weakness, nervousness, anxiety, agitation, irritability, dizziness, nasal congestion, fever, seating, hypoglycaemia, hot flushes, allergy, rash, cough, dry mouth, nausea, vomiting, decreased appetite, increased appetite, constipation and diarrhoea. Presence and severity of each item will be rated as absent, mild, moderate or severe.

Additionally, we will assess ophthalmological effects, by measures of visual acuity, contrast sensitivity and fundus photography. An ophthalmologist will perform grading of the photographs according to the EURODIAB study grading system [5, 44, 45].

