**Fig. 3 Fig3:**
[figure not shown]
Light spectral and relative intensity measures. Light spectral and relative intensity measures at 50 cm distance of the bright white-yellowish light condition (yellow), the dim green light condition (green) and the lamp without filter (blue)

Mania (in bipolar depressive patients) and acute suicidality have been theorised as potential psychiatric side effects of light therapy [24, 48, 49] although there is little documented evidence. The investigator will contact a participant weekly during the intervention in order to be able to intervene in case of deterioration of psychiatric symptoms.

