## Conclusions

If light therapy shows to be safe and effective in the reduction of depressive symptoms and improves insulin sensitivity, light therapy may be a valuable patient friendly addition to the currently available treatment strategies for major depression in T2D patients, assuming that improved insulin sensitivity may lead to improvements in glycaemic control, as measured by fasting glucose levels and HbA1c levels. Additionally, if our data support the role of restoration of circadian rhythmicity in these effects, such a finding may guide further development of chronobiological treatment strategies in these patients, as well as provide a basis for research into the effects of light therapy in other T2D patients, such as those without major depression but with sleep disorders.

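### The solicited adverse-effect list omits mania and suicidality, the two psychiatric side effects that the protocol itself names, and no other stated safety measure records them

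*Protocol article*

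**What the plan says.** In Methods/design, Safety, after the Fig. 3 caption, the protocol article states: "Mania (in bipolar depressive patients) and acute suicidality have been theorised as potential psychiatric side effects of light therapy". The sentence adds that the evidence for these effects is sparse. The stated response is: "The investigator will contact a participant weekly during the intervention in order to be able to intervene in case of deterioration of psychiatric symptoms".

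Under Safety and tolerability of light therapy, adverse effects are collected "using a self-report adverse effects questionnaire (T0, T1, T2, T3, T4, T8"). The article writes out the content of the form: "The following items will be assessed: tired eyes, dry eyes, painful eyes, visual impairment, headache", continuing to diarrhoea. Each item is rated on four levels, from absent to severe. The items nearest to psychiatric harm are "nervousness, anxiety, agitation, irritability, dizziness". One further safety measure follows: "Additionally, we will assess ophthalmological effects, by measures of visual acuity, contrast sensitivity and fundus photography". The Safety rows of Table 1 list the same two elements, adverse effects and an ophthalmological examination, and nothing else.

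The exclusion criteria list mania and severe acute suicidality. They do not list bipolar disorder. The Conclusions look ahead to a safety statement: "If light therapy shows to be safe and effective in the reduction of depressive symptoms".

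**The concern.** The protocol identifies two specific psychiatric harms and then specifies a solicited form that asks about neither. This contrasts with how it treats the eye. The ocular worry raised in the Safety section is carried through to visual acuity, contrast sensitivity and graded fundus photographs. The psychiatric worry raised in the same section leads to no stated measurement.

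What is at stake is how a clean safety result can be read. If harms are asked about in both arms on the same form at the same times, a low count is informative. If they are not asked about, a low count may only mean that nobody volunteered them. The article anticipates a conclusion about safety, and these are the only two psychiatric harms that it names. Sparse prior evidence does not excuse the omission; it is a reason to collect the data.

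**Working it through.** The plan states no figure on this point, so there is none to reproduce. The check is a count of the form's items and a comparison of sections.

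**Step 1: count the items on the form.** Grouped by content:
- ocular: tired eyes, dry eyes, painful eyes, visual impairment (4)
- sleep and energy: early morning awakening, fatigue, drowsiness, weakness (4)
- arousal and mood: nervousness, anxiety, agitation, irritability (4)
- other somatic, from headache to diarrhoea (17)

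Total: 4 + 4 + 4 + 17 = 29. Items for mania or elevated mood: 0. Items for suicidal thoughts: 0. The four arousal and mood items are non-specific; agitation or irritability can be rated without either named harm being present.

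**Step 2: follow each named harm through the article.**

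| Harm raised in the Safety section | Entry criterion | Stated safety measure |
|---|---|---|
| Ocular damage | Visual acuity and retinopathy exclusions | Visual acuity, contrast sensitivity, fundus photography; four ocular items on the form |
| Mania (bipolar patients) | Mania excluded; bipolar disorder not listed | None |
| Acute suicidality | Severe acute suicidality excluded | None |

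**Step 3: look for another recorded source.**
- *Weekly contact.* Its stated purposes are intervention (Safety) and adherence (Compliance). No instrument, rating or record is given. Table 1 shows telephone contacts at weeks 1, 2, 3 and 6, and visits at weeks 0, 4 and 8.
- *Inventory of Depressive Symptomatology (IDS).* It is completed at T0, T1, T2, T3, T4 and T8, the same schedule as the adverse-effect form. The article presents it as a primary efficacy outcome and does not list its items. It gives the scale no safety role and does not mention elevated mood in connection with it. Whether it contains a suicidality item cannot be settled from the article and is not relied on here.
- *Statistical analyses.* No analysis of adverse effects by arm is described.

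**Step 4: what added rows could and could not show.** Half of 98 participants is 49 per arm. With zero events among 49, the exact 95% upper limit is 1 − 0.05^(1/49) = 5.9% one-sided, or 1 − 0.025^(1/49) = 7.3% as the upper end of a two-sided interval. This shows only the precision available if all 49 were observed; it does not measure the omission. It also does not apply to mania, because the article places that risk in bipolar patients, whose number in the trial is unknown.

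**The case against.** The strongest reply is that a solicited side-effect form is not a trial's whole adverse-event system, and the article does not say that it is. The investigator is in weekly contact specifically with psychiatric deterioration in mind. The IDS is completed at the same time points. Serious and spontaneous adverse-event reporting is commonly left to a full protocol, which is not shown. A reader might infer from the item list that the trial cannot report mania or suicidality at all, or holds no structured data bearing on them. The article does not support either inference, and both should be set aside.

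Nor should these be called the psychiatric harms that the protocol thinks most likely. It calls them theorised, notes how little evidence there is, and confines mania to bipolar patients. Entry is also less open than the diagnosis alone suggests: there is a standardised psychiatric interview, two relevant exclusions, and a general exclusion for other medical conditions that could compromise effects or safety. How many bipolar patients would enter is uncertain. Finally, the article specifies no between-arm safety test that the omission could invalidate, and its remark on safety in the Conclusions is conditional.

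All of this limits the point without removing it. The article does not defer the content of the form; it lists the items, the scale and the time points. That list does not carry through what the Safety section says, and the contact that might fill the gap is not described as recording anything.

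**Conclusion.** The point holds in a limited form. The enumerated form covers 0 of the 2 psychiatric side effects that the protocol names, and no other stated safety measure covers them. Individual cases could come to light through the weekly contact or spontaneous reports. What is missing from the plan as described is systematic, solicited information, collected in the same way in both arms. A statement that light therapy is safe would therefore not rest on such information for mania or suicidality. It does not follow that these events would go undetected or unreported.

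The primary analyses and the sample size are unaffected, and no stated figure is wrong. The conclusion assumes that the printed list is the complete form and that no other recorded instrument is assigned to these effects. If one exists, naming it would largely resolve the point. How often either event would occur cannot be estimated from the article.

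**What to change.** Reconcile the Safety section with the section on safety and tolerability, in one of two ways:

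1. Add two rows to the existing questionnaire, one for abnormally elevated or overactive mood and one for suicidal thoughts, on the same four-level scale and at the same times (T0, T1, T2, T3, T4, T8). The T0 rating separates what was present before treatment from what appears later.
2. If another recorded instrument already captures either effect, name it and state that it will be used for safety reporting.

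In both cases, tabulate the two effects descriptively by arm, with the number of participants asked. Self-rated rows would give comparable counts of reported symptoms; nothing in the article shows that they would detect mania as a diagnosis, and the report should say so.

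The cost is a minor amendment, two more lines for participants at six time points, and answers that staff must read. Recruitment had begun in June 2014 and was still under way when the article was submitted, so participants who have already completed will lack the items; the report should disclose how many. Clinical handling of a case is outside this point.

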#### Compliance

Participants will note their compliance to therapy in a diary. Objective measures of compliance will be obtained from lux-meters built in a wrist-worn accelerometer.

### Sample size

A previous study on the effects of light therapy on depression in elderly patients using a comparable protocol [30] showed that direct treatment effects of light therapy on depressive symptoms were moderate (effect size 0.50 Cohen’s d), and increased during follow-up (effect size 0.91 Cohen’s d), with one-sided testing. Power calculations were based on the expected moderate effect size and a conservative repeated measures correlation of 0.6, using conventional values for α (0.05) and β (0.20), and two-tailed tests with equal groups – the sample size aimed for will be 42 participants per treatment arm. Accounting for an attrition rate of 15 %, we derive at a total sample size of 98 participants.

The question whether light therapy alters insulin sensitivity in type 2 diabetes patients with depression will be tested in a subsample of 60 participants in total. A sample size of 30 participants per treatment arm is sufficient to detect a moderate effect (0.76 Cohen’s d) of light therapy on insulin sensitivity, with conventional values for α (0.05) and β (0.20), and two-tailed tests with equal groups, assuming a dropout rate of 10 %. The hyperinsulinaemic-euglycaemic clamp experiment will thus be performed in a subgroup of the participants and participation in this procedure will be optional. Participants with difficult venous access or medical conditions that impair the safety of the procedure will be excluded from participation in the hyperinsulinaemic-euglycaemic clamp experiment.

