### Statistical analyses

Data will be analysed using SPSS (version to be determined). Participant and baseline characteristics across treatment groups will be compared using analysis of variance (ANOVA) and chi-squared statistics. Analyses of our primary outcome measures will be performed on the basis of intention to treat. The superiority of the bright white-yellowish light condition compared to dim green light condition will be tested using a repeated measures mixed models design. Both treatment (independent of time) and condition*time interaction effects will be evaluated. Repeated measures logistic regression will be applied to test differences in depression remission rates. Preacher and Hayes mediation analysis will be performed to test whether the effects of light therapy are mediated by restoration of the circadian rhythmicity. Post hoc analyses of this study may include subgroup or discriminant analysis to test if participant characteristics can be identified that predict positive effects of light therapy, such as baseline depression severity, baseline depressive symptoms profile, baseline insulin sensitivity, baseline HbA1c, chronotype, or baseline insomnia severity, seasonality of depression and time of year at which the participant was included in the study.

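### The sample size section does not say which IDS contrast the 42 per arm is for; under a stated assumption about the effect-size scale it gives about 81% power for T4 adjusted for T0, but about 72% for the unadjusted T0–T4 change

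*Protocol article*

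**What the plan says.** The Sample size section takes its effect from an earlier trial in elderly patients, where "direct treatment effects of light therapy on depressive symptoms were moderate (effect size 0.50 Cohen’s d") and larger at follow-up (0.91). It then says: "Power calculations were based on the expected moderate effect size and a conservative repeated measures correlation of 0.6". The significance level is 0.05, two-sided, with 80% power and arms of equal size, and the section concludes that "the sample size aimed for will be 42 participants per treatment arm". Allowing for 15% attrition, the total is 98. The section names no test, no number of visits and no formula.

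Two other sections describe the comparison:

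- Outcome measures: changes over T0–T4, T4–T8 or T0–T8 "will be compared between the two study conditions".
- Statistical analyses: superiority is tested with a repeated measures mixed model. "Both treatment (independent of time) and condition*time interaction effects will be evaluated".

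The IDS is collected at six visits (T0, T1, T2, T3, T4, T8). None of these sections mentions adjustment for the T0 score.

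**The concern.** A repeated measures correlation of 0.6 affects the required number very differently according to the contrast. It reduces the variance of a change score to 0.80 of that of a single-visit score, but the variance of a T4 score adjusted for T0 to 0.64. A sample size that is right for the second is too small for the first.

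The article gives one number and several possible contrasts without linking them. The effect it plans on is the direct effect of treatment, for which T0–T4 is the natural interval. If the analysis is an unadjusted comparison of T0–T4 change, the chance of missing the planned effect on a primary outcome is about 28% rather than 20%.

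**Working it through.** **Inputs.** From the Sample size section: d = 0.50, r = 0.6, two-sided α = 0.05, power 80%, 42 per arm. From the primary outcome section: six IDS visits. Assumptions: d is in single-visit SD units and, where more than two visits enter, every pair of visits has correlation 0.6 (compound symmetry).

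**Base number.** For an unadjusted comparison at one visit, n per arm = 2(1.960 + 0.842)² / 0.50² = 62.8. Each other contrast multiplies this by its variance factor, provided the effect on that contrast is still 0.50.

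**Reproducing 42.** Two routes arrive at it.

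- T4 adjusted for T0: factor 1 − r² = 1 − 0.36 = 0.64, and 62.8 × 0.64 = 40.2. This is 41 per arm by the normal approximation and 42 with the t distribution.
- Mean of six visits, unadjusted: factor (1 + 5 × 0.6)/6 = 0.667, and 62.8 × 0.667 = 41.9. This is 42 (normal) or 43 (t).

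**Unadjusted T0–T4 change.** Factor 2(1 − r) = 0.80, and 62.8 × 0.80 = 50.2, so 51 (normal) or 52 (t) per arm. At 42 per arm the non-centrality is 0.50/√0.80 × √(42/2) = 2.56.

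| Contrast (d = 0.50, r = 0.6, two-sided 0.05) | Power at 42 per arm, t | Normal |
|---|---|---|
| T4 adjusted for T0 | 80.8% | 81.7% |
| T0–T4 change, unadjusted | 71.6% | 72.6% |
| Single visit, unadjusted | 62.0% | 63.0% |

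If all 49 per arm completed, the unadjusted change would still have only 78% power (t).

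**Treatment effect independent of time.** The six-visit route to 42 needs the average effect to be 0.50, and therefore a difference of 0.50 at T0. Before the lamp is used, randomisation makes the expected difference zero. Power at 42 per arm (t) for realistic versions is:

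- Six visits, zero at T0 and the full 0.50 at all five later visits: the average effect is 0.50 × 5/6 = 0.417, the non-centrality is 0.417/√0.667 × √21 = 2.34, and power is about 64%.
- Five later visits only, full 0.50 at each from week 1: factor (1 + 4 × 0.6)/5 = 0.68, and power is about 78%.
- If the effect builds up linearly to 0.50 at T4 and holds to T8, the averages are 0.292 (six visits) and 0.350 (five visits), and power is about 37% and 48%.

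**Condition-by-time test.** Power at 42 per arm depends on the form of the test and on the trajectory.

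- Time as a category (5 df), linear build-up to 0.50 at T4, held to T8: about 72%.
- Linear trend over T0–T4 reaching 0.50 at T4 (1 df): the contrast has effect 1.25 and variance 10 × 0.4 = 4.0, so the non-centrality is 1.25/2 × √21 = 2.86 and power is about 81%.
- Time as a category (5 df), same build-up but 0.91 at T8: about 99%.

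**The case against.** The strongest reply is that 42 does reproduce from the article's own inputs under an analysis the article names. The treatment effect independent of time, over six visits, gives exactly 42 by the normal approximation, and the reference to a repeated measures correlation suits such a formula. This stands against any claim that 42 fits only a T0-adjusted analysis, and against calling 42 an arithmetic error. It does not secure 80% power, because the six-visit version requires a treatment effect before treatment. The nearest realistic version, five later visits with the full effect from the first week, gives about 78%.

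A second reply is that the sentence about comparing changes is general. It covers all outcomes and three intervals, and does not make T0–T4 the primary IDS test. That is fair. A reader might infer that the trial, run as written, carries a 28% risk of missing its planned effect. The documents do not support that without conditions: the mixed model leaves several contrasts open, a linear trend over T0–T4 reaches about 81%, and a follow-up effect of 0.91, as seen in the source trial, would take the 5-df interaction to about 99%. The article planned on 0.50, however, so 0.91 is not its planning value.

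Third, the scale of d is not stated. If 0.50 were in change-score SD units, the correlation would play no part and power for the change would be about 62% to 63%, lower rather than higher.

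Finally, how baseline enters a mixed model is often left to the analysis plan, so silence on a covariate is not in itself the fault. The point rests on what is printed: a sample size with no stated contrast, and a comparison of changes that it does not power at 80% on the assumed scale.

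**Conclusion.** The point holds in a conditional form. The 42 per arm is not tied to a contrast. With d = 0.50 in single-visit SD units, r = 0.6 and two-sided 0.05, it supports the T4 difference adjusted for T0 (about 81%) but not the unadjusted T0–T4 change (about 72%; 51 to 52 per arm for 80%). The time-averaged treatment effect does not rescue the stated power once T0 is treated as a baseline: about 64% with T0 among the responses, and about 78% at best over the five later visits. The condition-by-time test may fall short of or exceed 80%, depending on its form and the trajectory. The multi-visit figures also rest on compound symmetry.

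This is worth correcting because it concerns the power for a primary outcome and a better-powered contrast is available from data already collected.

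**What to change.** In Outcome measures and Statistical analyses, make the primary IDS contrast the between-arm difference at T4 adjusted for T0. Either enter the T0 IDS as a covariate with the post-baseline visits as responses, or keep T0 among the responses and constrain its mean to be equal across arms. In Sample size, state that 42 per arm assumes this contrast, and give the scale of the 0.50. If the unadjusted T0–T4 change is kept as the test, restate its power as about 72%.

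The cost is a few words in three sections. The T0 IDS is already collected, so no further participants or data are needed.
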